5.1.5.3 Minimum 2-hour Post-Dose Observation Period

- Subjects will remain in clinic for at least 2 hours post-vaccination.
- During the observation period in clinic, vital signs (BP, HR, RR and oral temperature will be taken/assessed hourly. Any unusual signs or symptoms reported during the initial 2 hours of observation will prompt continued close monitoring All data will be recorded in the source document during the post observation period.
- During the observation period, subjects will be provided a Memory Aid (MA), a template for measuring solicited local reactions and an oral digital thermometer to record daily temperature in degrees Celsius. The clinic staff will provide training to the subjects during this time. The subjects will be:
  - Instructed on how to measure their oral temperature with the digital thermometer supplied to them for purposes of the study. From the evening of Day 0 to Day 7 following each vaccination, temperature will be taken at approximately the same time each evening and the findings will be recorded in the MA.
  - Instructed by study staff on how to measure erythema (redness) and swelling 0-20 mm, 21-50 mm and > 50 mm diameter at the injection site using the simple template supplied and to evaluate pain at the injection site. Local tolerance reactions will be assessed every day starting from the evening the injection was administered on Day 0 and continuing and up to Day 7 following each vaccination and recorded on the MA.
  - Requested to grade, on a daily basis from the evening of Day 0 through to Day 7 following each vaccination, each of the solicited systemic reactions as described in Appendix A, the MA.
  - Requested to record their individual data in their MA as described above
  - Requested to use their MA to support their recall in providing information during the scheduled telephone interview conducted on Days 1 and 8 following each vaccination
  - Advised that they will be asked about the occurrence of any symptoms or events requiring medical attention and the use of concomitant medication during each 21-day post dose period as well as throughout the 160 day follow-up period
  - Requested to bring their MA to each clinic visit. The completed MA will not be collected by the study site.
  - Advised on emergency contact information and instructions for contacting study personnel. Subjects will be advised to immediately contact the Investigator, or his designee, in the event of a serious adverse event or medical emergency. Subjects will be provided with a telephone contact number and be instructed to call if any reaction to vaccination is significant or concerning.
  - Advised to notify their health care professional(s) (e.g., primary care physician) that they are participating in a clinical research study of an influenza vaccine.
  - Provided with a date and time to return to the clinic for the Day 21 and Day 42 follow-up visits.

5.1.5.4 Days 1 and 8 Telephone Contact (acceptable interval +/- 1 day), following vaccination 1 and 2)

- Subjects will be asked to use their MA to support their recall in providing information during the scheduled telephone interview conducted on Days 1 and 8 following each vaccination
- Telephone calls will be conducted at Days 22 and 29 (one and eight days following the second vaccination).
- The highest oral temperature, the greatest dimension of local redness and swelling, and the highest symptom grade experienced for each solicited local and systemic reaction from Day 0 to Day 1 and Day 2 – Day 7, will be ascertained and recorded.
- Unsolicited adverse events and/or solicited local and systemic reactions of greater than (>) grade 2 (moderate) severity will be reported promptly (24-48 hours) to the Investigator, who may request the subject come to the clinic for evaluation at his/her discretion. The Investigator will document review of these AEs on the source document.
- If any of the solicited local or systemic reactions noted at the Day 8 telephone contact persist beyond Day 7, these will be considered an AE. The subject will be requested to note when the AEs resolve and report this information to the Investigator or clinic staff at the Day 21 or Day 42 visit.
- Subjects will also be asked about any difficulties in completing the MA, any change in health, any visits to health care facilities and / or medical practitioners and use of any concomitant medications

The subject will be reminded of the date and time of their Day 21 and Day 42 visits.

- - - 1. Day 21 Visit, second vaccination, (acceptable interval +/- 2 days) and

Day 42, (acceptable interval +5 days)

The following procedures will be performed:

- Oral temperature in ºCelsius will be taken and recorded.
- Blood samples of approximately 20mL for biochemistry and haematology, 10mL for serologic testing and 20mL for cellular immune response assays will be taken.
- A urine pregnancy test on all female subjects of child-bearing potential.
- Subjects will be asked about any change in their health, any visits to health care facilities and / or medical practitioners and use of any concomitant medications
- Physical examinations will not be routinely performed at Day 21 or Day 42 visits, unless new complaints or concerns are raised by either the study subject or study staff, and if deemed to be necessary by the Investigator.
- On Day 21, subjects will be vaccinated in the same manner and with the same dose of vaccine (or placebo) that they received at the Dosing visit (Day 0).
- At the Day 21 visit, subjects will again be instructed to take and record their oral temperature on a daily basis for 7 days at approximately the same time each evening and the findings will be recorded in the MA. Subjects will be asked to take their temperature at any other time they feel feverish and to record the highest temperature of the day in the Memory Aid. If the subject becomes feverish (defined as a temperature of >38.0ºC degrees Celsius, they may take OTC antipyretics (acetaminophen, aspirin or ibuprofen) and will be advised to increase the frequency of their temperature measurements to approximately every four (4) hours, until no longer febrile.
- Provision of the subject with a new MA for the collection of solicited local and systemic events and any adverse events occurring following the Day 21 visit and a date and time for the Day 42 visit (Acceptable interval is + 5 days).
- Telephone calls will be conducted at Days 22 and 29 (one and eight days following the second vaccination).
- Provision of a new MA for collection of safety data at the Day 42 visit and a date and time for the final visit at Day 228.
- Monthly telephone calls for collection of adverse events or serious adverse events will be made to all subjects following the day 42 visit until the time of the final visit at Day 228.

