This safety data may be un-blinded based on the reviewers’ medical judgement.

Stopping rules or conditions for stopping this clinical trial would occur if there was clear evidence of harm or harmful side effects such as Serious Adverse Events related to the treatment (study vaccine). A Serious Adverse Event which was thought to be unrelated to the study vaccine would not warrant stopping the trial.

Based on the medical experts’ opinion, the following criteria may result in the stopping of the clinical trial:

- - - More than one (1) SAE probably related to the study vaccine.
    - Solicited Local injection site symptom reactions >grade 2 (moderate) severity = > 70%
    - Solicited Systemic symptom reactions > grade 2 (moderate) = > 50%

Refer to a sample outline of the safety narrative in Appendix C.

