**Table 2 STUDY CP-H5VLP-001 - Summary of Demographics and Baseline Characteristics**

Dose 1 or Dose 2 - Dose Level (1µg or 5µg)

| Parameter | n (%) |
| --- | --- |
| Age (years) – Mean (SD) |  |
| Gender = n (%) |  |
| Male |  |
| Female |  |
| Height (cm) – Mean (SD) |  |
| Weight (kg) – Mean (SD) |  |
| Race = n (%) |  |
| Caucasian |  |
| Black or African American |  |
| Asian |  |
| Ethnicity = n (%) |  |
| Hispanic or Latino |  |
| Not Hispanic or Latino |  |
| Received prior influenza immunization 24 months previously |  |
| Had Adverse reaction to prior influenza vaccine |  |

**Table 3 STUDY CP-H5VLP-001 Number and percentage incidence of solicited systemic reactions (Mild, Moderate, Severe) by symptom and day – Dose 1 or 2. Dose Level (1µg or 5µg)**

| Symptom | 2-6 hours post vaccination  n (%) | Day 0  Evening  n (%) | Day 1  n (%) | Day 2  n (%) | Day 3  n (%) | Day 4  n (%) | Day 5  n (%) | Day 6  n (%) | Day 7  n (%) | Total  n (%) |
| --- | --- | --- | --- | --- | --- | --- | --- | --- | --- | --- |
| Fever (Mild, Moderate or Severe) |  |  |  |  |  |  |  |  |  |  |
| Muscle Aches |  |  |  |  |  |  |  |  |  |  |
| Joint Aches |  |  |  |  |  |  |  |  |  |  |
| Fatigue |  |  |  |  |  |  |  |  |  |  |
| Chills |  |  |  |  |  |  |  |  |  |  |
| Malaise (uneasiness and discomfort) |  |  |  |  |  |  |  |  |  |  |
| Swelling of the neck |  |  |  |  |  |  |  |  |  |  |
| Swelling of the groin (R./L) |  |  |  |  |  |  |  |  |  |  |
| Swelling of the axilla (R/L) |  |  |  |  |  |  |  |  |  |  |
| Swelling of the chest |  |  |  |  |  |  |  |  |  |  |

**Table 4. STUDY CP-H5VLP-001 Number and incidence of mild/moderate/severe solicited local reactions by symptom and day – Dose 1**

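### Home temperature is taken once each evening after dose 1 but also on feeling feverish after dose 2, so fever is ascertained less sensitively in the data that gate escalation

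*Protocol*

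**What the plan says.** **Dose 1.** Section 5.1.5.3, the training given at the first dosing visit, sets the home rule: "From the evening of Day 0 to Day 7 following each vaccination, temperature will be taken at approximately the same time each evening". It asks for nothing beyond that daily reading.

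**Dose 2.** The section on the Day 21 and Day 42 visits (5.1.5.5 in the table of contents) repeats the evening reading and adds to it: "Subjects will be asked to take their temperature at any other time they feel feverish and to record the highest temperature of the day". A subject who becomes feverish, "defined as a temperature of >38.0ºC degrees Celsius", is also "advised to increase the frequency of their temperature measurements to approximately every four (4) hours, until no longer febrile".

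**Telephone calls.** Section 5.1.5.4 covers both doses. The value taken down for Day 0–1 and for Day 2–7 is "The highest oral temperature, the greatest dimension of local redness and swelling", together with the highest symptom grades.

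**Memory Aid.** Appendix A has one temperature cell per day in degrees Celsius. It does not ask for the day's highest temperature, although it does ask for the worst grade of each symptom in the past 24 hours. Fever is not among its graded rows.

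**Escalation.** Under section 5.1.2, a favourable 7-day report on Cohort 1 after the first dose allows vaccination of Cohort 2 at 10 µg.

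**Grading.** Section 2.1.1 lists fever among the solicited systemic symptoms, but the graded list in section 8.1.1.1 leaves it out. Appendix C, Table 3, has a row "Fever (Mild, Moderate or Severe", and section 9.1.8 includes the criterion "Solicited Systemic symptom reactions > grade 2 (moderate) = > 50" per cent.

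**The concern.** Fever is part of the primary safety endpoint. A single evening reading can miss a fever that rises and settles between evenings, whereas prompted readings with the daily maximum recorded would catch more of them. As written, the more sensitive method starts only at dose 2.

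Two things are at stake. The panel that decides on escalation sees dose-1 data collected by the weaker method. And anyone who sets fever after dose 1 beside fever after dose 2 will see a difference that comes partly from how temperature was taken.

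A smaller matter sits beside this. Subjects are told to grade each solicited systemic reaction as set out in the Memory Aid, which offers no fever grade. The report table asks for one, and both the stopping criterion and the prompt report to the investigator (5.1.5.4 and 9.1.1) turn on reactions above grade 2.

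**Working it through.** **1. Do the two instructions differ?** Yes. The evening reading is common to both doses. Readings on feeling feverish, recording of the day's highest value and the four-hourly step-up appear only in the Day 21 section, and nothing extends them to dose 1. The call's highest temperature does not close the gap. After dose 1 it is the highest of the evening readings, apart from the clinic readings in the first 2 hours and any reading a subject happens to take unasked.

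**2. Do dose-1 data gate escalation?** For 5 to 10 µg, yes, by section 5.1.2. For 10 to 20 µg, the text is less explicit and Figure 2 came through with a broken layout, so this step is read with care. The figure appears to place Cohort 3's start at about Days 24–27, Cohort 1's second vaccination at about Days 21–24 and Cohort 2's at about Days 33–36. The first Cohort 1 subject would complete 7 days after dose 2 at 21 + 7 = Day 28, after Cohort 3 has started. The only Cohort 2 review shown is its first.

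**3. The protocol's own figure.** Section 11.3 gives the chance of observing a reaction at least once in 12 subjects:

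- P = 1 − (1 − p)^12
- p = 0.10: 1 − 0.90^12 = 71.8% (stated: about 72%)
- p = 0.05: 1 − 0.95^12 = 46.0% (stated: about 46%)

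Both reproduce. They take for granted that every reaction that occurs is recorded.

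**4. Illustration of incomplete capture.** Let s be the share of febrile subjects caught by evening readings alone. The documents give no value, so s is an assumption and a range is shown. Replace p by p × s:

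| s (assumed) | p = 0.10 | p = 0.05 |
|---|---|---|
| 1.0 | 71.8% | 46.0% |
| 0.8 | 1 − 0.92^12 = 63.2% | 1 − 0.96^12 = 38.7% |
| 0.7 | 1 − 0.93^12 = 58.1% | 1 − 0.965^12 = 34.8% |
| 0.5 | 1 − 0.95^12 = 46.0% | 1 − 0.975^12 = 26.2% |

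At s = 0.5, a 10% fever rate is no easier to see than a fully recorded 5% rate.

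**5. Dose 1 beside dose 2.** Take a true rate of 10% after both doses in the 36 vaccinees, with full capture after dose 2 (also an assumption). Expected febrile subjects after dose 2: 36 × 0.10 = 3.6. After dose 1: 36 × 0.10 × 0.8 = 2.9, or 36 × 0.10 × 0.5 = 1.8. The apparent rise comes from measurement alone.

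**6. The planned test.** Section 11.1.2.2 compares each dose level with placebo. Within a dose, both arms follow the same rule. If s is equal in the arms, the observed difference is s × p(vaccine) − s × p(placebo) = s × [p(vaccine) − p(placebo)]. The absolute difference shrinks and events are lost, but neither arm is favoured.

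**The case against.** The strongest reply is that this is a drafting omission and not a chosen design. The Day 21 text says subjects are instructed again, as if repeating one procedure in more detail, and the call script seeks the highest temperature after either dose. That is plausible. But a site trains subjects from the text it has, and the dose-1 text lacks the extra readings. A probable oversight is a reason to correct it.

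The second reply is that fever is not hidden from the reviewers. Sections 5.1.1 and 9.1.8 give them the oral temperatures for the first seven days, chills and malaise are graded daily, and the stopping criteria rest on the medical experts' opinion. This stands and limits the consequence, though the temperatures supplied after dose 1 are still those of the evening schedule.

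Third, Appendix C is labelled a sample, its tables still carry placeholder dose levels, and fever bands for tabulation could sit in the analysis plan. That tempers the grading point. The mismatch among the diary, the endpoint list and the report table is nevertheless within this protocol.

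A reader might go further and infer a two- to four-fold spurious rise, for example by assuming fevers of 6 to 12 hours with onset spread evenly over the day. The documents give no episode length or onset pattern, and onset after an injection need not be uniform. A reader might also infer that a rise after dose 2 would be taken for sensitisation. The protocol says nothing of the kind, and the placebo arm would show the same shift in ascertainment.

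**Conclusion.** The instructions differ by dose, and fever is ascertained less sensitively after dose 1 as the protocol is written. That dose supplies the 7-day report for the step from 5 to 10 µg and, if Figure 2 is read correctly, for the step from 10 to 20 µg.

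Only the direction of the loss follows from the text. The fall from about 72% to 63%–46% in the chance of seeing at least one fever in 12, at 10% true incidence, depends on the assumed capture of 80% to 50%.

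It would be too strong to say that the two doses cannot be compared at all, or that the planned analysis is biased. No test of dose 1 against dose 2 is planned. A descriptive comparison would be confounded by ascertainment, while the contrast with placebo stays fair between arms.

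The grading mismatch is real but secondary. It would also be too strong to say that fever can never count toward the criterion for reactions above grade 2: sections 9.1.1 and 9.1.6 define severity by limitation of activity, and the criterion is discretionary. What is missing is any stated link from a recorded temperature to a grade.

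**What to change.** Put one measuring and recording instruction in section 5.1.5.3, to apply identically after both doses: the evening reading, extra readings whenever the subject feels feverish, and the day's highest value written down. Print it on the Memory Aid beside the temperature row, and refer to it from the Day 21 section. State whether the four-hourly step-up also covers both doses. The antipyretic advice in the same place is clinical management, and nothing is proposed on it.

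Separately, reconcile section 8.1.1.1 and Appendices A and B, where fever has no grade, with section 9.1.8 and Appendix C, where fever is tabulated as mild, moderate or severe and reactions above grade 2 are counted. Either cite the sponsor's fever scale or state that fever is not graded. No threshold is proposed here.

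The cost is protocol and diary wording; subjects already receive a thermometer. The downside is that slightly more fever will be recorded after dose 1.

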5.1.5.6 Final Visit - Day 228 (Acceptable interval is +14days)

The following procedures will be performed:

- A blood sample of approximately 10mL will be drawn for influenza serology testing to evaluate antibody persistence for approximately 6 months following vaccination. A final 20 mL blood sample will also be collected for cellular immune assay analysis. For females of child-bearing potential, a urine pregnancy analysis will be performed.
- Study subjects will be asked to bring their MAs to the visit and will be asked about any change in their health, any visits to health care facilities and / or medical practitioners and use of any concomitant medications since the last contact.

5.2 Discussion of the Trial Design

This study is a randomized, partially double-blind, placebo-controlled, dose-escalation study evaluating two doses, 21 days apart and three dose levels of plant-based H5 VLP (H5N1) influenza vaccine compared to the placebo, 100mM phosphate buffer + 150mM NaCl + 0.01% Tween 80 combined with Alhydrogel® (aluminium hydroxide) in study subjects 18 – 60 years of age.

5.3 Selection of the Trial Population

5.3.1 Recruitment Procedures

Subjects enrolled in this study will be healthy adults, aged 18 to 60 years and will be volunteer members of the community at large. Following IRB approval, potential subjects will be contacted and will be invited to participate in this trial, if they meet all inclusion criteria and do not meet any exclusion criteria.

5.3.2 Participant Information and Consent

Voluntary written informed consent must be obtained from each subject prior to performing any study-related procedures. Each subject should be given both verbal and written information describing the nature and duration of the clinical study. The informed consent process should take place under conditions where the subject has adequate time to consider the risks and benefits associated with his/her participation in the study. Subjects should not be screened or treated until they have signed an approved informed consent form written in a language that is understandable to the subject.

The Independent Research Ethics Committee (IEC/IRB) approved informed consent form should be signed and dated by the subject and the physician (or their nominated designee) who conducted the informed consent discussion. Each subject should receive a copy of the signed and dated written informed consent form along with any other written information provided to the subject.

The Investigator is responsible for assuring the appropriate content of the informed consent form and that informed consent is obtained from each subject in accordance with all applicable regulations and guidelines. The original signed informed consent form should be retained in the Investigator’s files.

The Investigator should maintain a log of all subjects who sign the informed consent form and indicate if the subject received study drug or, if not, the reason why. The subject’s available medical records should also document that the informed consent form was signed and dated prior to any study-related procedures being performed.

5.3.5 Temporary Contraindications

- Temperature >38.0ºC.
- Acute cold symptoms such as minor URTI symptoms that typically resolve in 48-72 hours.

5.3.6 Removal of Participants from Treatment or Assessment

Subjects will be advised that they are free to withdraw from the study at any time without prejudice to their future medical care by the physician or the institution. Subjects who withdraw or are withdrawn from the study after dosing will not be replaced. The primary reason for withdrawal must be recorded in the subject’s medical record and captured in the CRF.

5.3.6.1 Conditions for Withdrawal

Every reasonable effort should be made to ensure that each subject complies with the protocol and completes all study visits. However, a subject may withdraw or be withdrawn from participation if:

- The subject withdraws consent, or
- In the opinion of the Investigator the subject displays non-compliance to the terms of their participation in the clinical trial, or
- Safety reasons as judged by the Investigator and / or Medicago R&D Inc., or
- BGTD, Health Canada or the IRB/IEC terminates the clinical trial.

In case of withdrawal due to a serious adverse event, a subject will not be replaced. Drop-outs will be those subjects who leave the study earlier than planned for whatever reason; drop-outs will not be replaced. Drop-outs who receive at least one dose of study medication will be asked to return to the study site for a final assessment. All drop-outs must be reported to Medicago R&D Inc. The reason for drop-out should be documented in the subjects’ records and in the appropriate section of the CRF. The CRF must be completed up to and including the time of drop-out/final assessment.

5.3.6.2 Lost to Follow-up Procedures

Every attempt will be made to contact study subjects who are lost to follow-up. At least 3 telephone contacts will be attempted and recorded in the source document. As a last resort, one registered letter requesting contact with the site will be sent to any subject with whom the clinic staff no longer has contact.

5.3.6.3 Screen Failures

Screen failures are subjects that have signed the Informed Consent Form, but who were not randomized due to failure on one or more inclusion or exclusion criteria. Eligible/not treated subjects are subjects that have signed the Informed Consent Form and are eligible for enrolment, but were either not randomized or randomized and not treated. Tracking of both classes of screen failures will be carried out by the completion of the demography and termination CRF pages. Neither class of subjects will receive a safety follow-up.

